**1. Introduction**

Oral mucositis (OM) is one of the most common adverse events during chemotherapy and affects quality of life of patients receiving chemotherapy in relation to the dose of drugs. However, there is only one drug (palifermin) approved by the US FDA for the prevention of OM and the other methods to prevent or treat OM are just empirical and lack evidences. The results of recent study demonstrated promising efficacy and minimal toxicity of recombinant human epidermal growth factor (rhEGF) as a preventive drug of OM in head and neck cancer patients undergoing radiotherapy (Wu HG, et al. Cancer 2009;115(16):3699-3708). This clinical trial is a double-blind, randomised, prospective, single-institutional, phase II study to evaluate efficacy and toxicity of rhEGF as a preventive drug of OM during intensive chemotherapy with stem cell transplantation in patients with hematologic malignancies.

**2. Study eligibility criteria**

1. Inclusion criteria

- Patients with more than 18 years of age
- Patients with confirmed diagnosis of hematologic malignancies including acute & chronic leukemia, lymphoma, plasma cell dyscrasia, myelodysplastic syndrome, aplastic anemia, etc.
- Patients who are planned to receive high-dose chemotherapy with hematopoietic stem cell transplantation
- ECOG performance status of 0-2
- Informed consent

1. Exclusion criteria

- Patients having previous history of hypersensitivity to this drug or similar drugs
- Patients having oral ulcer or herpes at the time of inclusion
- Patients having severe dental disease at the time of inclusion
- Patients received chemotherapy or radiotherapy within 3 weeks
- Patients received surgery within 3 weeks
- Patients who had finished clinical trials which could affect the results of this trial within 4 weeks or are attending one at the time of inclusion
- Patients having another diseases which have worse prognosis than patients' hematologic malignancy
- Patients with major psychotic disorder or drug/alcohol abuser
- Women who are pregnant or breastfeeding
- Inappropriate patients according to the investigators' opinion
- Refusal at patients' will

**3. Study endpoints**

1. Primary endpoint

- Incidence of OM of grade 2 or higher (NCI CTCAE [common terminology criteria for adverse events] 3.0)

1. Secondary endpoints

- Day of onset and duration of OM of grade 2 or higher (NCI CTCAE 3.0)
- Incidence, day of onset, and duration of OM of grade 3 or higher (NCI CTCAE 3.0)
- Incidence, day of onset, and duration of OM of grade 2 or higher (WHO OM scoring system scale)
- Incidence, day of onset, and duration of OM of grade 3 or higher (WHO OM scoring system scale)
- Incidence, day of onset, and duration of OM of grade 4 or higher (WHO OM scoring system scale)
- OM daily questionnaire (OMDQ) score during treatment
- Duration of opioid analgesics use
- Side effects and safety evaluation of rhEGF
- Adverse events

**4. Statistics (including power calculations)**

1. Study design

Double blind, placebo-controlled, randomised method, single-centre study

[figure not shown]

Figure 1. Study design and schedule. HSCT, Hematopoietic Stem Cell Transplantation; Treatment Group A, recombinant human epidermal growth factor (E); Treatment Group B, placebo (P).

1. Sample size calculation

This study is designed to test the hypothesis that the incidence of NCI grade ≥2 OM would be 37% (H1), which is significantly different from 64% of previously published data. This study is designed to have 80% power to detect 27% improvement in the incidence of NCI grade ≥2 OM in the rhEGF group as compared with placebo, at a two-sided alpha level of 0.05. If patients are randomised at 1:1 ratio, to reject H0, at least 62 patients are required in each treatment group. Assuming a 10% dropout rate, the total number of patients needed for this study is 138 patients - 69 patients per each group.

| **Numeric Results for Two-Sided Test of Proportions. Continuity Correction Applied.**  **Power N1 N2 Alpha Beta P1 P2**  0.806915 62 62 0.050000 0.193085 0.37 0.64 |
| --- |

1. Randomisation

- Patients will be randomly assigned to the rhEGF or placebo group at a 1:1 ratio using computer-generated randomisation by the Medical Research Collaborating Center (MRCC), Seoul National University Hospital (Seoul, Republic of Korea), which is not involved in the data analysis. The study is double blinded, thus all clinicians, patients, and investigators assessing outcomes, and analysing data are masked to treatment assignment. The placebo is compounded with all the ingredients of the rhEGF preparation except for rhEGF, and is supplied in a masked manner for patients.

1. Administration of study drugs

- Dose of investigational products
  - Patients are instructed to spray rhEGF or placebo over their entire oral mucosa twice daily.
- Methods of administration
  - For each application, patients spray total 6 times at palate, oropharynx, both buccal mucosa, tongue, and gingiva. Oral intake is restricted 30 minutes after administration.
- Duration of administration
  - Application of drugs begins with start of intensive chemotherapy and ends at the time of recovery from neutropenia (ANC>1000/µL for 3 days) or disappearance of oral mucositis.

1. Clinical data collection

- Assessment of OM severity
  - OM severity is assessed once during screening period and every day during administration period.
  - A qualified researcher grades the severity of OM using the following two scales: the NCI CTCAE ver. 3.0 and the WHO oral mucositis scoring system scale.
- Self-assessment of mouth and throat soreness and swallowing difficulty
  - Patient-reported quality of life during the study period is evaluated daily using a modified version of the Oral Mucositis Daily Questionnaire (OMDQ).
- Medical records
  - Concomitant medications including total parenteral nutrition (TPN), opioid analgesics, and antibiotics are recorded in the case report form every day.
  - In case of infection, causative organisms, severity, duration, and treatment methods are recorded in the case report form.
  - Transplant-related complications such as acute graft-versus-host disease and veno-occlusive disease are recorded in the case report form along with their severity, duration, and treatment methods.
- Advese events
  - Treatment-related adverse events are monitored every day.
  - In case of adverse event development, related information such as date of onset, severity, relationship with investigational products, and treatment methods is recorded and evaluated.
  - Serious adverse events are reported to clinical trial review board.
- Compliance
  - Patient compliance is assessed through daily confirmation of patient-documented administration records.
  - (Compliance) = (Actual administration by patient) / (Scheduled administration)

1. Principles of data analysis

The final data will be analysed on an intent-to-treat (ITT) basis for primary and secondary endpoints. In addition, per protocol analysis will be performed for patients whose compliance for study drugs is more than 75%. The t-test and Mann-Whitney U test will be used to compare parametric and non-parametric continuous variables, respectively. Categorical variables will be compared using the Pearson’s chi-square test or the Fisher’s exact test, as appropriate.

1. Interim analysis

Interim analysis is planned at the time of study design using the O’Brien-Fleming type alpha spending function by Lan and Demets (1983). If the interim analysis is performed when 50% of patients were enrolled, an alpha level of 0.003 should be used to reject H0.

| **Details when Spending = O'Brien-Fleming, N1 = 62, N2 =62, P1 = 0.37, P2 = 0.64,**  **Continuity Correction.**  **Lower Upper Nominal Inc Total Inc Total**  **Look Time Bndry Bndry Alpha Alpha Alpha Power Power**  1 0.50 -2.96259 2.96259 0.003051 0.003051 0.003051 0.168499 0.168499  2 1.00 -1.96857 1.96857 0.049002 0.046949 0.050000 0.638415 0.806915 |
| --- |

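### Oral mucositis is graded only during drug administration, whose end is ambiguous and may be set by the outcome itself, so durations may be cut short and some first grade ≥2 episodes missed

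*Protocol*

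**What the plan says.** Three parts of the protocol meet here.

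- **Grading window** (section 4, Clinical data collection): "OM severity is assessed once during screening period and every day during administration period". The readable text states no later grading and no fixed last day.
- **End of administration** (section 4, Administration of study drugs): use of the spray begins with intensive chemotherapy and "ends at the time of recovery from neutropenia (ANC>1000/µL for 3 days) or disappearance of oral mucositis". It is not said whether the earlier or the later event applies.
- **Endpoints and analysis** (section 3; section 4, Principles of data analysis): the primary endpoint is the incidence of NCI grade ≥2 OM. Duration is a secondary endpoint at five thresholds: NCI ≥2 and ≥3, and WHO ≥2, ≥3 and ≥4. None has a time window. On the analysis set: "The final data will be analysed on an intent-to-treat (ITT) basis for primary and secondary endpoints". Continuous variables are compared by t-test or Mann-Whitney test.

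**The concern.** Observation of the outcome is tied to use of the drug, and one of the two events that end use of the drug is the outcome itself ("or disappearance of oral mucositis"). If the earlier event governs, the time for which a patient is graded depends on how fast the mouth heals, and healing is what rhEGF is meant to change. The arms would then be compared over windows that treatment can lengthen or shorten.

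The two possible biases need not point the same way. Cutting durations at neutrophil recovery removes more days from the arm with longer OM, so it hides a real benefit. Closing the window when mild OM clears could lower the observed incidence more in an arm that clears mild OM faster, and so suggest prevention that did not occur. An analysis plan can choose how to handle missing grades, but it cannot recover grades that were never taken.

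**Working it through.** **1. The plan's own figure.** The sample size reproduces, so the point does not rest on an arithmetic error. Inputs from section 4: 0.37 v 0.64, 62 per arm, two-sided 0.05, continuity correction. With pooled variance:

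(0.27 − 1/62) / √(0.505 × 0.495 × 2/62) − 1.96 = 0.2539/0.0898 − 1.96 ≈ 0.867, so power is 0.807, against 0.806915 stated.

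Dropout: 62/0.9 = 68.9, so 69 per arm and 138 in total, as stated.

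**2. Each clinical course under the two readings.**

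| Course | Earlier event governs | Later event governs |
|---|---|---|
| Grade ≥2 reached while grading continues | Counted | Counted |
| OM still present at neutrophil recovery | Duration cut off that day | Graded until OM disappears |
| Grade ≥2 OM clears before neutrophil recovery | Duration of that episode complete | Complete |
| Mild OM clears during neutropenia, first grade ≥2 episode follows | Not counted | Counted if it begins before neutrophil recovery |
| Patient stops spraying early without an event | No grading stated after the stop | No grading stated after the stop |

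The second and fourth rows carry the bias, and both depend on the earlier-event reading. The last row arises under either reading if the administration period means actual use.

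**3. Duration, earlier-event reading.** The protocol gives no timing, so every input here is assumed: onset uniform on days 6–12; gamma durations with mean 9 days (placebo) and 6 days (rhEGF); neutrophil recovery normal with SD 3 days. Recorded duration = min(true duration, recovery day − onset day), for patients with onset before recovery. The true difference is 9 − 6 = 3 days. Difference recorded, in days:

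| Gamma shape | Recovery day 14 | Day 16 | Day 18 |
|---|---|---|---|
| 1 | 0.6 | 0.8 | 1.0 |
| 2 | 0.6 | 0.9 | 1.3 |
| 4 | 0.7 | 1.1 | 1.5 |

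For shape 4 and day 16 the recorded means are about 5.8 and 4.8 days. Across the grid, half or more of the benefit is lost. The t-test and Mann-Whitney test treat a cut-off duration as complete.

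**4. Incidence, earlier-event reading.** The share of events missed is also assumed.

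- *Unequal loss, no true effect.* With 64% in both arms and 10% (rhEGF) v 5% (placebo) of events missed: 0.64 × 0.90 = 57.6% and 0.64 × 0.95 = 60.8%, a spurious 3.2 points. At 69 per arm, two-sided rejection rises from about 5% to about 6% (exact, uncorrected chi-square).
- *Equal loss at the design rates.* With 10% of events missed in both arms: 0.37 × 0.90 = 33.3% and 0.64 × 0.90 = 57.6%, a difference of 24.3 points. Continuity-corrected power at 69 per arm falls from 0.86 to 0.78.

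**The case against.** The strongest reply is that the later-event reading is equally natural: patients without OM stop at neutrophil recovery, and those with OM continue until it has gone. On that reading the duration and incidence problems largely disappear for patients who stay on schedule. This stands, and it is why the bias is stated conditionally.

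The administration period can also be read as a study phase, in contrast to the screening period. Compliance is defined against scheduled administration, so a schedule exists apart from actual spraying, and grading might continue after a patient stops. Figure 1 (design and schedule) is not shown and could carry later assessments. Both are possible. Even so, a scheduled phase would still end at one of the same two events, so the ambiguity remains.

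The missed-episode route is narrow as well. Mild OM must appear, clear completely during neutropenia and be followed by a first grade ≥2 episode. The protocol gives no frequency for this. The duration example is also demanding: at shape 4 and day 16 it implies that about 62% (placebo) and 40% (rhEGF) of cases persist at neutrophil recovery.

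A reader might infer more than the documents support:

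- *That the intent-to-treat analysis cannot be done.* It can. Every patient can be analysed as randomised, and those who reached grade ≥2 before stopping are already events. Only event-free early stoppers are incomplete, and rules for them may sit in an analysis plan that is not shown.
- *That the 10% dropout allowance measures the loss.* It is a sample-size allowance, not a rate of stopping the spray, and patients who leave the trial are ungraded under any window. Best-case and worst-case bounds on those 69 − 62 = 7 patients per arm are not evidence for this point.
- *That the questionnaire and opioid endpoints share the defect.* The endpoint "OM daily questionnaire (OMDQ) score during treatment" is compatible with daily collection over the study period, since one can contain the other. Opioid use is recorded every day, with no stated tie to dosing.

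**Conclusion.** The point holds in a conditional form. As written, OM grading is tied to drug administration, the end of administration is ambiguous, and one of the two events that end it is the outcome itself. Under the earlier-event reading, durations are cut off at neutrophil recovery and some first grade ≥2 episodes can be missed. Under the later-event reading most of this goes away, leaving possibly incomplete outcomes for event-free early stoppers.

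The size cannot be determined from the protocol. A 3-day duration benefit recorded as about 0.6 to 1.5 days rests wholly on the assumed timings and on the earlier-event reading. The effect on the primary endpoint may be small: the 10% v 5% example adds about one percentage point to the type I error. The point deserves correction because grades not collected cannot be restored at analysis and the remedy is cheap, not because a large bias has been shown.

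**What to change.** Separate assessment from dosing. Continue the same daily OM grading, on both scales, in every randomised patient who remains available, whether or not study drug is still used. Run it to one end point defined identically in both arms, for example a fixed transplant day, or OM resolution if later. Define incidence and duration over that window.

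The two drug-stop criteria under Administration of study drugs must be reconciled with each other and with the assessment schedule, so that all staff apply them alike. Which criterion should govern is a clinical matter, and no dosing rule is proposed here.

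The cost is protocol wording and some additional days of bedside grading by the same researcher. No further patients are needed, and the stated sample size does not change.

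### The intent-to-treat rule covers the safety endpoints, so randomised patients who never used the spray stay in the adverse event denominators; the bias is probably small but understates harm

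*Protocol*

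**What the plan says.** Two parts of the protocol have to be read together.

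- Section 3 (Study endpoints) includes "Side effects and safety evaluation of rhEGF" in the list of secondary endpoints, with adverse events as a further item in the same list.
- Section 4, under the principles of data analysis, states: "The final data will be analysed on an intent-to-treat (ITT) basis for primary and secondary endpoints". Safety is not exempted.

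The same paragraph of section 4 names one other analysis set: "per protocol analysis will be performed for patients whose compliance for study drugs is more than 75" (per cent). Compliance is the number of administrations the patient actually made divided by the number scheduled. The protocol names no set made up of patients who received the product at least once, and none grouped by product received.

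The Introduction gives efficacy and toxicity as the two things the trial evaluates.

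**The concern.** Intent-to-treat is the usual basis for efficacy because it preserves the randomised comparison. For harm caused by a product, the relevant denominator is the patients who were exposed to it. A patient randomised to rhEGF who leaves before the first spray adds one to the denominator and cannot add a product-caused event to the numerator. The product-caused rate is pulled down, and so is the excess over placebo.

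This is a rule the protocol states, not a detail left open: safety is a secondary endpoint, and secondary endpoints are assigned to intent-to-treat. What is at stake is the toxicity aim of a phase II trial, where the planned denominator can only make the product look safer.

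**Working it through.** **Inputs from the protocol.** At least 62 patients are required per group, with 10% dropout and 69 per group (section 4, sample size calculation): "Assuming a 10% dropout rate, the total number of patients needed for this study is 138 patients - 69 patients per each group".

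**Reproducing the plan's figure.** 62 / 0.90 = 68.9, rounded up to 69 per group; 2 × 69 = 138. This agrees with the protocol. The point challenges no figure in the plan.

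**Inputs the protocol does not give (assumed here).**
- The never-dosed share f. I take 7 of 69 as a ceiling (10% of 69 = 6.9, so the entire dropout is treated as undosed) and 2 of 69 as a milder case, with f equal in both arms.
- The event rates in dosed patients. I take 20% on rhEGF and 10% on placebo, for illustration only.
- The event rate u in undosed patients. I show u = 0 and u = 10%.

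**Formula.** Rate seen under intent-to-treat = (1 − f) × rate in dosed patients + f × u.

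If f and u are the same in both arms, the u terms cancel in the difference:

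Difference seen = (1 − f) × (rhEGF rate − placebo rate in dosed patients).

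So the excess over placebo shrinks by (1 − f) whatever u is. The rates themselves shrink by (1 − f) only when u = 0. That is the case for events caused by the product, or if undosed patients contribute no events because, for example, they are not followed.

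**Results.**

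| Undosed per arm | 1 − f | u | rhEGF rate seen | Placebo rate seen | Difference seen |
|---|---|---|---|---|---|
| 0 of 69 | 1 | – | 20.0% | 10.0% | 10.0 points |
| 2 of 69 | 67/69 = 0.97 | 0 | 13.4/69 = 19.4% | 6.7/69 = 9.7% | 9.7 points |
| 2 of 69 | 0.97 | 10% | (13.4 + 0.2)/69 = 19.7% | 10.0% | 9.7 points |
| 7 of 69 | 62/69 = 0.90 | 0 | 12.4/69 = 18.0% | 6.2/69 = 9.0% | 9.0 points |
| 7 of 69 | 0.90 | 10% | (12.4 + 0.7)/69 = 19.0% | (6.2 + 0.7)/69 = 10.0% | 9.0 points |

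The u = 10% rows matter because these patients are planned for high-dose chemotherapy with transplant. Someone who declines the spray but goes on to transplant still has the adverse events of that treatment. For adverse events of any cause, the ceiling case is then about 19% against 10%, not 18% against 9%.

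**The case against.** Four objections deserve an answer.

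**A safety set is usually defined in the SAP, which is not at hand.** This would be decisive if the protocol were silent. It is not: its wording assigns a set to these endpoints, and a SAP that used a treated set would depart from it. What stands is that the mere absence of a safety set definition is not the finding; the reach of the intent-to-treat sentence is.

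**The effect is small.** This stands. The protocol does not say that any dropout is undosed, and the spray starts with the chemotherapy, so f may be close to zero and intent-to-treat close to an analysis of treated patients. Even at the ceiling the difference moves by 1 point, while its standard error at 69 per arm is √[(0.18 × 0.82 + 0.09 × 0.91)/69] = 0.058, or 5.8 points. The bias is less than a fifth of that. It would not by itself produce a finding of minimal toxicity.

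**The compliance set.** A reader might infer that safety will also be judged in the set with compliance above 75%, that this set drops patients who stop because they cannot tolerate rhEGF, and that both sets therefore push toward no difference. The text does not support going that far. The per-protocol analysis is described as additional, and no endpoints are named for it. Whether an early stopper falls below 75% depends on what counts as scheduled after stopping, which is not defined; planned dosing "ends at the time of recovery from neutropenia (ANC>1000/µL for 3 days) or disappearance of oral mucositis". Placebo contains every ingredient except rhEGF, so intolerance of the vehicle could exclude patients from both arms, as could mucositis itself. Size and direction are unknown. What stands is only that this set is no suitable substitute for a safety set, since it could exclude patients who stop for intolerance.

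**Wrong supply.** A reader might also infer that rhEGF events will be counted under placebo because of dispensing errors. Nothing in the protocol suggests that such errors are expected.

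**Conclusion.** The point holds in a limited form. As written, the protocol analyses side effects and adverse events in all randomised patients, including any who were never given the spray. This multiplies product-caused event rates, and the excess over placebo, by (1 − f). The factor is 0.90 if the whole 10% dropout is undosed and 0.97 if 2 of 69 are. The first figure is an assumed ceiling, because the protocol gives neither the undosed share nor any adverse event rate. The result for the excess also assumes the same undosed share, and the same event rate among undosed patients, in both arms.

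The bias is probably small and its direction is toward understating harm. It would be too strong to say that every adverse event rate falls by 10%, since background events need not be diluted, or that neither planned set can measure toxicity, since intent-to-treat comes close when few patients are undosed. The change is worth making because toxicity is a stated aim and the correction is almost free. The primary endpoint, sample size and alpha are untouched.

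**What to change.** In section 4, principles of data analysis, limit the intent-to-treat sentence to the primary endpoint and the secondary efficacy endpoints. Then add wording such as: Side effects and adverse events will be analysed in all patients who received at least one application of study product, grouped by the product actually received.

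It would also help to say that the set with compliance above 75% is not used for safety.

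The cost is about one sentence. No new data are needed, because the administration records are already confirmed daily and show who was dosed. Reported event rates may come out slightly higher.

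### The primary test is fixed as unadjusted although entry is open to any stem cell transplant; a test stratified by planned transplant type would be a cheap improvement, not the repair of an error

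*Protocol*

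**What the plan says.** All places are in the Protocol.

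- **Section 2, inclusion criteria.** Entry covers "Patients who are planned to receive high-dose chemotherapy with hematopoietic stem cell transplantation". The listed diseases run from acute and chronic leukaemia through lymphoma and plasma cell dyscrasia to myelodysplastic syndrome and aplastic anaemia. No transplant type is named and none is excluded.
- **Section 4, Randomisation.** "Patients will be randomly assigned to the rhEGF or placebo group at a 1:1 ratio using computer-generated randomisation", run by an independent centre. No stratification factor, block or minimisation is mentioned.
- **Section 4, Clinical data collection.** "Transplant-related complications such as acute graft-versus-host disease and veno-occlusive disease are recorded". The first of these complications points to allogeneic transplants.
- **Section 4, Principles of data analysis.** "Categorical variables will be compared using the" Pearson chi-square or Fisher exact test, as appropriate. The primary endpoint (section 3: incidence of oral mucositis of NCI grade 2 or higher) is a categorical variable, so this is its test. No covariate or stratum is named.

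**The concern.** Planned transplant type is known for every patient before the first application of study drug, and it may be related to the risk of mucositis. If it is, two things follow. First, a chance difference between the arms in the share of allogeneic patients moves the estimated treatment difference, and the planned test makes no adjustment for it. Second, the variation between transplant types stays in the error term, so some power is lost. An adjustment added after the data are unblinded would be open to dispute. This is one single-centre trial, with no second study to average out an unlucky draw.

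**Working it through.** **1. The plan's own figure.** Inputs from section 4, Sample size calculation: 37% vs 64%, "at a two-sided alpha level of 0.05", "at least 62 patients are required in each treatment group". The interim table gives boundaries 2.96259 and 1.96857.

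- Pooled rate = (0.37 + 0.64)/2 = 0.505.
- SE = √(2 × 0.505 × 0.495 / 62) = 0.0898.
- Continuity-corrected drift = (0.27 − 1/62)/0.0898 = 2.83.
- Two-look power with the stated boundaries = 0.806 (stated 0.8069); first-look power 0.168 (stated 0.1685); overall alpha 0.050.
- Dropout: 62/0.9 = 68.9, so 69 per arm and 138 in total.

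The stated design reproduces.

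**2. How likely is a chance imbalance?** Assume that half the patients are allogeneic and that allocation is simple 1:1 with 69 per arm.

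- SD of the difference in allogeneic share = √(2 × 0.5 × 0.5 / 69) = 0.0851.
- At least 10 points: 0.10/0.0851 = 1.17, two-sided probability 24%.
- At least 15 points: 0.15/0.0851 = 1.76, probability 7.8%.
- If 30% rather than 50% are allogeneic: SD 0.078, and the 10-point probability is 20%.

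**3. What does an imbalance do?** The shift is the imbalance times the risk gap between transplant types. With an assumed 30-point gap, 10 points of imbalance shift the difference by 0.10 × 30 = 3 points, and 15 points shift it by 4.5, against a planned 27. The standard error of the difference at 69 per arm is about 8.2 points and already includes this source of variation.

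**4. Power over a range of gaps.** Simulation with 200,000 trials per scenario, 69 per arm, half allogeneic, simple randomisation, a common odds ratio with marginal rates held at 0.64 and 0.37, a single look at critical value 1.96857, and no continuity correction in either test:

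| Assumed gap in placebo risk | Pearson | CMH |
|---|---|---|
| 0 points | 0.895 | 0.892 |
| 20 points | 0.897 | 0.906 |
| 30 points | 0.895 | 0.920 |
| 40 points | 0.896 | 0.942 |

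Type I error was 0.048 to 0.049 for both tests. With both tests continuity-corrected, the 30-point row becomes 0.860 vs 0.889, a gain of about the same size.

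**5. One unlucky draw.** Suppose 40 of 69 rhEGF patients and 29 of 69 placebo patients are in the high-risk stratum, a difference of about 16 points. At a 30-point gap, power given that draw is about 0.76 for Pearson and 0.91 for CMH. With no treatment effect, the rejection rates are about 0.075 and 0.049. These figures are conditional on the draw; averaged over all draws, Pearson returns to step 4.

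**6. If transplant type is not prognostic.** At 69 per arm the loss is 0.895 − 0.892, under half a point. At 62 per arm it is about 2 points (0.878 vs 0.855). At 65 per arm there is none (0.866 vs 0.870). The differences come largely from the discreteness of the tests.

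**7. If the randomisation is in fact stratified by a prognostic factor.** The unadjusted chi-square then ignores the strata and is conservative. Its simulated alpha is about 0.037 to 0.042 at a 30-point gap.

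**The case against.** The strongest reply is that nothing here is wrong. An unadjusted chi-square after 1:1 randomisation is valid, and chance imbalance averages to zero and is already inside its standard error. **This stands.** A reader might infer from step 3 that the result would be biased by several points, or that type I error is not controlled. Neither follows, because the shift in step 3 is not an extra error on top of the stated one.

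The second reply is that the protocol's silence has been read as fact. **This also stands.** A reader might conclude that the randomisation is unstratified, but the text only names no factor, and strata may sit in a randomisation document. A demand to change the list would therefore be unsupported. Likewise, autologous and allogeneic transplants are never named. Their joint inclusion is inferred from open eligibility and from the recording of graft-versus-host disease.

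The third reply is that the link to risk is undocumented. **This stands.** The Introduction speaks of drug dose, not transplant type, and every risk gap used here is assumed.

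The fourth reply is that the gain is small and may vanish. **This stands only in part.** At a 20-point gap the gain is about 1 point at 69 per arm, and at 62 per arm there is none (0.877 vs 0.872). A finding of no gain at a 30-point gap arises only when a continuity-corrected CMH is set against an uncorrected Pearson; like for like, there is a gain.

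Nor can the matter simply be left to an analysis plan. The protocol names the test, and a plan that made an adjusted test primary would depart from it.

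**Conclusion.** The point holds as a recommended improvement, not as an error. The planned test is valid, the sample size reproduces, and the unadjusted analysis meets its goal: "This study is designed to have 80% power to detect 27% improvement". It would be wrong to call the trial underpowered or its test biased.

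What remains is a choice that could be better. At 69 per arm the stratified test changes power by about −0.3, +1, +2.5 and +4.6 points at assumed gaps of 0, 20, 30 and 40 points. It also protects the one trial to be run against a 10-point imbalance that has a probability of about 24%. These sizes rest on an assumed half-and-half split, simple randomisation and assumed risk gaps, none of which the documents give. At gaps of 20 points or less the case rests mainly on protection against an unlucky draw, not on power.

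**What to change.** Before anyone sees unblinded data, including at the interim analysis, amend Principles of data analysis:

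1. Make the primary test a CMH test without continuity correction, stratified by planned transplant type (autologous vs allogeneic) as recorded before treatment starts.
2. Report a stratified risk difference with its 95% CI.
3. Keep the unadjusted chi-square as a sensitivity analysis.
4. State in the Randomisation section whether allocation is stratified and by what. If it is stratified by a prognostic factor, use that factor in the primary test.

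The cost is a few sentences and one baseline variable. No change to the sample size or the randomisation list is needed. If transplant type turns out not to be prognostic, the loss lies between nothing and about 2 points of power, depending on the exact number analysed. Power stays above the 80% target (0.855 at 62 per arm).
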